#### Safety endpoint

2.11.2

The hyperpigmented spots are relatively expected events for this type of treatment and will be assessed by objective measurement in the same manner as previously described in the section “Efficacy Outcome.” Still as primary objective, safety, hyperpigmented spots will be objectively measured using the ImageJ software, and the comparison will be with the length of the telangiectasias before the treatment. The same examiners will make these analyzes as previously described.

#### Secondary outcomes

2.11.3

All the situations that may be indirectly involved with the results in terms of efficacy and safety, among them volume of drug used, number of punctures, skin color, and pain related to the treatment, will be analyzed in the secondary endpoints. Other adverse events as mild allergies, localized or diffuse edema, cough, mild lipothymia, hematomas and phlebitis, besides major adverse events such as syncope, DVT, severe allergies or other major health injuries will also be evaluated, as secondary endpoints.

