### Selection, inclusion, randomization, and masking

2.3

The sample will be of convenience, starting with a random and temporal list of patients who wish to do aesthetic treatment with sclerotherapy in the lower extremities due to mild venous disease - CEAP C1, in our institution. The patients will be invited by telephone to participate in the study, following the order of established by consulting the electronic database of our institution. They will be invited to attend a scheduled outpatient visit for clinical evaluation, and in order to be informed about the working methods. In this screening evaluation, patients who present telangiectasia on the lateral side of the thigh will then be invited to participate in the study and sign the ICF.

The inclusion will be random, using a spreadsheet electronically generated by the web-based free-access computer program Stat Trek (http://stattrek.com/Tables/Random.aspx). The patients will be randomized in 2 groups; one will receive treatment with 0.2% polidocanol diluted in glucose 70%; the other will be treated with glucose 75%. A trained nurse will generate and store all data in an opaque envelope for the entire duration of the study and prepare the solutions that will be used in the treatments, with sequential allocation in accordance with the order of addition. The solutions will be prepared in a medication room (different from the treatment room); the product (5 mL) will be drawn a sterile syringe identified only with the patient's protocol number, a few minutes before use, in such a way that the physician who will perform the procedure will have no contact with this phase of the research. It is noteworthy that the 2 drugs are colorless and odorless, with similar viscosity, what will promote an efficient blinding. Thus, all study participants will be blinded, patients, care providers, outcome assessors, and data analysts (triple blinded).

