### Pretreatment details

2.5

The patients will be included if they present telangiectasia not related to varicose veins on the side of the thigh of one of the lower extremities. The clinical diagnosis will be confirmed before treatment by duplex ultrasonography. Clinical data such as comorbidities, demographics and other relevant information will be compiled in specific forms for further analysis. All patients who do not meet the inclusion criteria during the screening evaluation will be referred to the routine outpatient clinic.

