### Treatment (D0)

2.8

After the photographic record of the first visit (D0), all patients will be treated similarly, aiming to eliminate all telangiectasia of the target area. The same physician will perform all the procedures. The treatment technique will be the conventional one, consisting of careful direct puncture of the telangiectasias in order to avoid infiltration of the subcutaneous tissue. The procedure will be conducted until the telangiectasias are undetectable. The maximum volume allowed by puncture will not exceed 0.3 mL. A plastic syringe, luer lock tip, with 3 mL will be used to apply the solution (BD), and the needle will be 13 × 0.4 mm (Terumo - or 27G ^1/2^ inch). The punctures will be occluded with a small cotton ball and a square piece of microporus surgical tape.

All events during the treatment will be recorded in this visit, including the amount of agent used for the disappearance of telangiectasias, possible allergic reactions, and others. Soon after the session, the patient will be invited to answer a questionnaire with questions related to discomfort or pain triggered by the treatment, that was already used in a previous similar study (Fig. 2).^[18]^

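### Skin colour is listed among the secondary outcomes; it belongs with the baseline characteristics, and adjusting the hyperpigmentation comparison for it would be a cheap gain in precision

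*Protocol article*

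**What the plan says.** Section 2.11.3 (Secondary outcomes) opens with "All the situations that may be indirectly involved with the results in terms of efficacy and safety", gives examples, and states that "volume of drug used, number of punctures, skin color, and pain related to the treatment, will be analyzed in the secondary endpoints". So one sentence describes the items as possible influences on the results and also places them among the endpoints.

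Section 2.11.2 (Safety endpoint) raises hyperpigmentation to primary status: "Still as primary objective, safety, hyperpigmented spots will be objectively measured using the ImageJ software". Its only reference quantity is baseline vessel length: "the comparison will be with the length of the telangiectasias before the treatment". Skin colour is not mentioned there.

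Section 2.12 (Statistical analysis) names Student's t test, the Mann–Whitney test, the chi-square or Fisher's exact test, and the Goodman association test. It gives no covariate and no regression model.

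Section 2.8 (Treatment (D0)) records the treatment session, "including the amount of agent used for the disappearance of telangiectasias", and sets a visual end point: "The procedure will be conducted until the telangiectasias are undetectable".

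Section 2.5 (Pretreatment details) says "Clinical data such as comorbidities, demographics and other relevant information will be compiled in specific forms for further analysis". It does not name skin colour. Section 2.3 says "The patients will be randomized in 2 groups" and mentions no stratification by skin colour.

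**The concern.** An outcome is something that the randomised treatment might change. Volume, puncture count and pain qualify. A patient's skin colour does not. If treatment-related discolouration was meant, the hyperpigmentation endpoint already covers it. On either reading, skin colour is out of place under Secondary outcomes.

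What is at stake is modest. The investigators themselves name skin colour as possibly involved with efficacy and safety, but the plan gives it no usable role. A baseline variable related to the response can narrow the confidence interval for the arm difference. Here that would benefit a primary safety objective, using a variable that the trial already intends to analyse. Naming the adjusted analysis in advance also prevents a later choice among unadjusted, adjusted and subgroup results.

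A secondary point is that the sentence puts skin colour on the same footing as volume and punctures. Those two arise after randomisation. Injection continues until no vessels can be seen, so both can depend on how well the assigned solution works. They should not be adjusted for alongside skin colour.

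**Working it through.** **1. The plan's own figure.** Section 2.12 gives alpha 0.05, SD 1.5, difference 0.9, 48 per arm and power above 80%. Sidedness is not stated; two-sided is assumed here.
- Standardised difference: 0.9 / 1.5 = 0.6.
- Normal approximation: 0.6 × √(48/2) = 2.94; 2.94 − 1.96 = 0.98; power = Φ(0.98) = 83.6%.
- Noncentral t: 82.9%.

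The stated power is reproduced. Skin colour plays no part in it, so this point leaves the sample size as it is.

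**2. Role of each listed item.**

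| Item | When it arises | Can the solution affect it? | Role |
|---|---|---|---|
| Volume used | Treatment session (2.8) | Yes, treated to a visual end point | Outcome |
| Number of punctures | Treatment session (2.8) | Yes, same reason | Outcome |
| Pain | Questionnaire after the session (2.8) | Yes | Outcome |
| Skin colour | Not stated; a patient trait | Not expected | Baseline characteristic |

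**3. What adjustment could gain.** In a linear model with a covariate that correlates ρ with the response within arms, residual variance is multiplied by (1 − ρ²), and the standard error of the arm difference by √(1 − ρ²). The document gives no ρ, so a range is assumed.

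| Assumed ρ | Fall in residual variance (ρ²) | Standard error multiplied by | Unadjusted limbs per arm giving the same precision as 48 |
|---|---|---|---|
| 0.3 | 9% | √0.91 = 0.954 | 48 / 0.91 = 52.7 |
| 0.5 | 25% | √0.75 = 0.866 | 48 / 0.75 = 64.0 |

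Three limits apply to this table.
- The 48 per arm was set for a primary endpoint score. The document gives no SD or rate for hyperpigmentation, so the last column only restates the variance ratio.
- With D0 length also in the model, ρ is the correlation that remains after D0 length has been accounted for.
- The formula belongs to a linear model and does not carry over directly to the Mann–Whitney test.

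**The case against.** The strongest reply is that this is a loose heading and little more. The sentence can be read as announcing an exploratory look at contributing factors. An unadjusted comparison of randomised arms is valid, and adjustment for a prognostic trait is an option for precision. Covariates are often left to an analysis plan, and none is shown. Nothing in the document says that skin colour predicts hyperpigmentation, when it is assessed, or on what scale. Hyperpigmentation is already related to baseline vessel length.

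Most of that stands, and it rules out four stronger readings that a reader might infer:
- *The hyperpigmentation comparison is biased.* It is not. Randomisation protects the unadjusted test.
- *Skin colour will be tested between arms as an outcome.* The document never says so explicitly. Such a test would be significant in about 5% of trials by chance and would say nothing about the solutions, but its use here is hypothetical.
- *The arm comparison will be adjusted for volume or punctures.* No stated analysis does this, since section 2.12 contains no adjusted model.
- *Skin colour is the main driver of hyperpigmentation.* No passage supports this.

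What the reply does not remove is the placement itself. The document lists a patient trait under Secondary outcomes, calls it possibly involved with the results, and names only tests that cannot use it in that role. This comes from what the text states and does not depend on an unseen plan.

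**Conclusion.** The point holds as a misplacement and a missed gain in precision. Skin colour should not stand among the secondary outcomes, and prespecified adjustment would sharpen a primary safety comparison if skin colour is related to hyperpigmentation. The gain cannot be computed from the document. The 9 to 25% fall in residual variance rests on an assumed correlation of 0.3 to 0.5 in a linear model; if the correlation is near zero, the gain is near zero as well. That skin colour is a baseline trait is a sensible inference, because the document does not say when it is recorded. The validity of the unadjusted comparison, the sample size and the primary efficacy test are unaffected.

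**What to change.** 1. Record skin colour before treatment on a stated scale, and move it from section 2.11.3 to the baseline characteristics.
2. In section 2.12, prespecify a between-arm analysis of hyperpigmented length adjusted for skin colour and D0 telangiectasia length, for example ANCOVA, or a rank-based equivalent if its assumptions fail.
3. Keep volume, punctures and pain as outcomes compared between arms.
4. As a safeguard, state that volume and punctures arise after randomisation and are not adjusted for in the main efficacy and safety comparisons.

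The cost is a few lines of text and slightly more analysis work. No extra patients or visits are needed. Skin colour is already due to be analysed, so the only possible addition to data collection is to fix that it is recorded before treatment.

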### Statistical analysis

2.12

Based on alpha = 0.05, and assuming a standard deviation in the primary endpoint score of 1.5, with 48 participants in each arm, we have >80% power to detect a minimum difference in scores of 0.9. Only 1 extremity will be included per patient and the analysis will be conducted comparing results per patients. It is expected that 10–20% of patients will be lost during follow-up. To promote the most statistically rigorous method, we will use a larger sample size of at least 115 patients. Data will be evaluated either by Student's *t* test or nonparametric Mann–Whitney test (if relevant conditions are not met). Categorical variables (e.g., proportions) will be compared between groups using the χ 2 or Fisher's exact test when necessary. Scores between the groups will be compared with Mann–Whitney test. Multiple comparisons between and within multinomial populations will be analyzed by Goodman association test. All statistical analyzes will be conducted using STATA v11 software (Stata Corp, College Station, TX). All analyses will be performed on an intent-to-treat basis.

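### Section 2.12 does not fix one test or one effect measure for the primary efficacy endpoint

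*Protocol article*

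**What the plan says.** All the text on the primary test is in section 2.12 (Statistical analysis) of the protocol article. Four statements bear on it.

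- The sample size is set by "assuming a standard deviation in the primary endpoint score of 1.5", "with 48 participants in each arm", with more than 80% power "to detect a minimum difference in scores of 0.9". This is a calculation on means. It calls the primary endpoint a score and gives no unit.
- Data, with no outcome specified, are evaluated by Student's t test "or nonparametric Mann–Whitney test (if relevant conditions are not met"). The conditions are not named.
- Two sentences later: "Scores between the groups will be compared with Mann–Whitney test". No condition is attached.
- No sentence says which of these rules governs the primary endpoint, or which effect measure will be reported.

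Section 2.11.1 (Efficacy endpoint) defines the primary outcome as telangiectasia length in centimetres, D0 against D60, averaged over two examiners. It says that absolute values will be compared, but not whether these are residual length, change or percent change.

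**The concern.** By the article's own vocabulary the primary endpoint is a score, so the unconditional Mann–Whitney sentence reaches it. By its definition in section 2.11.1 it is a continuous length, so the conditional t-or-Mann–Whitney sentence reaches it too. A reader cannot tell which applies.

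The two tests do not address the same quantity. The t test compares means, which is what the sample size was built on. Mann–Whitney compares the chance that a patient in one arm has a larger value than a patient in the other. That corresponds to a difference in means only under extra conditions, such as two distributions that differ by a pure shift. Under the conditional rule, the quantity behind the primary p-value is settled only once the distribution has been seen.

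The second branch is a realistic prospect. Residual length cannot fall below zero, and section 2.8 aims to eliminate every telangiectasia in the target area, so values bunched near zero are plausible.

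**Working it through.** **Inputs.** From section 2.12: alpha 0.05 (sidedness not stated; two-sided assumed), SD 1.5, difference 0.9, 48 per arm. Assumed, because the article gives no distribution and no check: normal or exponential data, and a Shapiro–Wilk test at 0.05 in either arm as the trigger for Mann–Whitney.

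**Step 1: the stated power.** Power = Φ(δ / (σ√(2/n)) − 1.96).

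- σ√(2/n) = 1.5 × √(2/48) = 0.306
- 0.9 / 0.306 = 2.939, and 2.939 − 1.96 = 0.979
- Φ(0.979) = 83.6%

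The noncentral t gives 82.9%. The claim of more than 80% reproduces.

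**Step 2: power if Mann–Whitney is the fixed test.** Multiply n by the asymptotic relative efficiency against the t test.

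- Normal data, efficiency 3/π: effective n = 48 × 0.955 = 45.8, power 81.9% (80.8% by simulation).
- Worst case, efficiency 0.864: effective n = 48 × 0.864 = 41.5, power 78.0%.

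With either test fixed, 48 per arm is broadly adequate.

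**Step 3: behaviour of the rules.** 20,000 simulated trials per row, 48 per arm. Entries are the percentage of trials significant at 0.05; the last column is the percentage in which one test is significant and the other is not.

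| Assumed data | t test | Mann–Whitney | Pre-test rule | Tests disagree |
|---|---|---|---|---|
| Normal, no effect | 5.0 | 5.0 | 5.1 | 2.1 |
| Normal, shift 0.9 | 82.9 | 80.8 | 82.6 | 4.9 |
| Exponential (SD 1.5), no effect | 5.0 | 4.8 | 4.8 | 4.0 |
| Exponential (SD 1.5), shift 0.9 | 82.9 | 97.8 | 97.8 | 14.9 |
| Equal means: exponential against normal, SD 1.5 each | 5.4 | 10.4 | 10.4 | 8.2 |

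The simulation standard error at 5% is √(0.05 × 0.95 / 20,000) = 0.15 percentage points, so 5.1% cannot be told apart from 5%. A separate simulation gave 5.0–5.2% for the pre-test rule, and disagreement of about 4% for normal and 15% for exponential data.

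**Step 4: what the last row shows.** The arms have the same mean and differ only in shape. The t test rejects at close to its nominal rate, while Mann–Whitney rejects about twice as often. This is not a fault in Mann–Whitney: the two tests have different null hypotheses, and the choice of test decides which hypothesis the trial has tested.

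**Step 5: the two readings of scores.**

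| If scores means | Rules reaching the primary endpoint | Result |
|---|---|---|
| Any outcome the section calls a score, including the primary | Unconditional Mann–Whitney and conditional t-or-Mann–Whitney | Two rules that disagree whenever the conditions are met |
| The pain questionnaire only | Conditional t-or-Mann–Whitney | No conflict, but the data choose the test |

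Neither reading gives one test and one effect measure.

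**The case against.** The strongest reply is that section 2.12 reads as a list by data type: continuous data, categorical variables, scores and multinomial populations, each with its own method. The primary endpoint is a measured length, so it belongs with the first. The trial also has a patient questionnaire on pain and discomfort (sections 2.8 and 2.11.3), which may be what scores refers to. This is a fair reading, and on it there is no direct contradiction. A reader might infer that the plan flatly contradicts itself, but the text supports only an ambiguity. The reply does not dispose of the point, because the primary length measure then falls wholly under the data-dependent rule.

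A second reply is that the two-branch rule is itself specified in advance, is triggered by fit to test conditions and not by the result, and will be applied by blinded analysts (section 2.3). This stands as far as error control goes. A reader might infer inflation to 6–7%. Simulation does give 6.0% (normal) and 6.9% (exponential) if the smaller of the two p-values is reported, but nothing in the article permits that. Blinding does not settle which quantity is estimated.

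A third reply is that the details of the check belong in a statistical analysis plan, and a condensed article may omit them. That is right for the name of the normality test or its threshold, and their absence is not the criticism. The article is not silent on the test: it states rules, and those rules leave the primary analysis open.

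**Conclusion.** The point holds as a matter of ambiguity. Section 2.12 does not tie the primary endpoint to one test or one effect measure, although the trial is sized on a mean difference.

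Its practical size is the share of trials in which the choice of test would change the conclusion at 0.05: about 4–5% with normal data and about 15% with exponential data, under a true shift of 0.9 and 48 per arm. These shapes are assumptions. More skewed assumptions can give more, around 20%, but no distribution in the article supports a particular figure.

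Two stronger conclusions do not follow. Type I error of the rule as written is about 5%. The sample size is not undermined either: the stated power reproduces, and with Mann–Whitney fixed it is 81–82% for normal data and 78.0% in the worst case. The matter should be corrected, but it does not threaten the design.

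**What to change.** In section 2.12, for the primary endpoint:

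1. Delete the conditional rule and name one analysis before unblinding. The preferred choice is ANCOVA of D60 length on treatment and D0 length with robust standard errors, reporting the adjusted mean difference with a 95% confidence interval. It matches the mean-based sample size and uses the D0 length already collected. It also removes the question of residual length or change, because with D0 length in the model both give the same treatment coefficient.
2. Keep Mann–Whitney as a sensitivity analysis, and state that it does not decide the result.
3. State which outcomes scores covers, for example the pain questionnaire, and use another word for the primary endpoint in the sample-size sentence.

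The cost is a few sentences, with no operational change. If a statistical analysis plan already fixes the primary test, the article need only be aligned with it.

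The downside is power under strong skew. In the exponential example the t test kept 82.9%, while Mann–Whitney reached 97.8%. Baseline adjustment would recover part of that gap, by an amount that depends on the correlation of D0 with D60 length, which the article does not give. Fixing either named test in advance would also cure the ambiguity, provided the effect measure is named with it.

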Some papers point out that the sclerosing power of polidocanol and sodium tetradecyl sulfate (STS) would be higher than hyperosmolar agents;^[10–12]^ however, both are more fluid and can flow to unwanted vessels. Those opposed to the use of polidocanol, warn against adverse effects such as tissue necrosis, allergic reactions, anaphylaxis, increased risk of deep venous thrombosis (DVT), pulmonary embolism (PE), scotoma, and gas embolization (when used in foam form).^[13]^ These events are rare and often related to miscalculated doses.^[14,15]^ Some minor adverse events such as hyperpigmented spots, as well as mild systemic adverse events such as coughing, brief scotoma, light lipothymia, are described as being more often associated with the use of polidocanol.^[16]^ On the other hand, other authors believe that the side effects can be avoided if the volume and infusion time are well calculated, therefore rendering better results without a higher rate of adverse events.^[17]^

A commercial presentation of polidocanol 0.2% diluted in glucose 70% has been used in Brazil with apparent success and safety but with no scientific proof. In a pilot study of this institution, there was a trend toward better results with the use of this solution, justifying, therefore, what we intend to test in this study, comparing the solution of polidocanol 0.2% diluted in glucose 70% to glucose 75% solution for the treatment of lower limbs telangiectasia.

The hypothesis to be tested is that the polidocanol 0.2% diluted in glucose 70% is more efficient than glucose 75% in eliminating lower limbs telangiectasia (efficacy). Differences in safety will also be investigated (minor and major adverse events).

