### Ethics approval and consent to participate

2.2

This study will be conducted in accordance to the principles of the Declaration of Helsinki, ISO14155, Data Protection Act, and guidelines for Good Clinical Practice. The Research Ethics Committee (REC) of the Botucatu Medical School, UNESP, São Paulo, Brazil, has approved this study, which was registered under the number 4127–2012 (see REC, supplemental digital content 1). During the screening visit, all patients will be fully informed of the benefits and risks of the study and the principal investigator will obtain the signature of the free and informed consent form (ICF) for all participants, before enrollment (see ICF, supplemental digital content 2). The subjects may leave this study at any point in time without any constraint, whenever they will.

All data will be sent to the ethics committee in the end of the study or if occur any major adverse effect. As the study provides a unique intervention, you can not interrupt the treatment.

The ClinicalTrials.gov identifier for this study is NCT02657252, obtained on January 12, 2016 (Acronym PG3T).

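### The intention-to-treat rule covers every analysis, so any patient not injected, or injected with the other solution, would be counted in the harm comparison under the allocated solution

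*Protocol article*

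**What the plan says.** Section 2.12 (Statistical analysis) sets one population rule for the whole trial: "All analyses will be performed on an intent-to-treat basis". The article as shown names no treated-patient or as-treated set.

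The rule reaches every harm comparison:

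- Section 2.11.2 (Safety endpoint) places pigmentation in the primary objective: "Still as primary objective, safety, hyperpigmented spots will be objectively measured using the ImageJ software".
- Section 2.11.3 (Secondary outcomes) adds treatment pain, minor adverse events, and "besides major adverse events such as syncope, DVT, severe allergies or other major health injuries will also be evaluated, as secondary endpoints".
- The Background states the aim as looking for a difference: "Differences in safety will also be investigated (minor and major adverse events"). No non-inferiority margin is given.

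On allocation and delivery, section 2.3 has a nurse prepare each syringe, labelled with the protocol number alone, "with sequential allocation in accordance with the order of addition". Section 2.2 notes that "The subjects may leave this study at any point in time without any constraint". Treatment is a single session (section 2.2), and one physician performs all procedures (section 2.8).

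**The concern.** For efficacy, analysis as randomised is the cautious choice, because deviations usually make two treatments look more alike. For harm the same tendency works the other way: a shrunken difference looks reassuring. Section 2.13 reports a somewhat higher frequency of mild adverse events, and rare serious ones, with polidocanol, so this is a comparison where shrinkage would favour the test product.

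Two kinds of patient would matter. One is allocated but never injected, and so cannot be harmed by either solution. The other is injected with the solution of the opposite arm, so that any harm is charged to the wrong product. Section 2.3 describes both solutions as clear, without smell and of like viscosity, with physician and patient blinded, so a mix-up would be hard to see at the bedside. The article mentions no record of the product actually drawn.

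**Working it through.** **The plan's own figure.** Section 2.12 says: "Based on alpha = 0.05, and assuming a standard deviation in the primary endpoint score of 1.5", with 48 per arm, a difference of 0.9 and more than 80% power. Sidedness is not stated; two-sided is assumed. The standard error is 1.5 × √(2/48) = 0.306, so 0.9/0.306 = 2.94 and power = Φ(2.94 − 1.96) = 83.6% (82.9% by the exact t test). The claim reproduces and does not depend on the present point.

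**Dilution factor.** Let h₁ and h₂ be the mean harm (a length or a risk) under the two solutions. In each arm let u be the share never injected, counted as zero harm, and m the share given the other solution.

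- Arm 1 as randomised: (1 − u − m)h₁ + m·h₂
- Arm 2 as randomised: (1 − u − m)h₂ + m·h₁
- Difference: (1 − u − 2m)(h₁ − h₂)

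**Inputs.** The document gives neither u nor m, and no effect size or standard deviation for pigmentation. All values of u and m below are assumptions. The power column borrows the efficacy values (0.9, 1.5, 48 per arm) only to give a scale.

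| u | m | 1 − u − 2m | Power on that scale |
|---|---|---|---|
| 0 | 0 | 1.00 | 83.6% |
| 1% | 1% | 0.97 | 81.4% |
| 2% | 2% | 0.94 | 78.9% |
| 5% | 0 | 0.95 | 79.7% |
| 5% | 5% | 0.85 | 70.5% |
| 10% | 5% | 0.80 | 65.2% |

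With assumed risks of 20% and 10%, the row at 2% and 2% gives 0.96 × 0.20 + 0.02 × 0.10 = 0.194 against 0.96 × 0.10 + 0.02 × 0.20 = 0.100. The difference is 9.4 points instead of 10. With 115 patients, 1% is about one patient (115 × 0.01 = 1.15) and 2% about two (2.3).

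**If the never-injected have no harm measurement.** They then drop out instead of counting as zero, and the factor becomes 1 − 2m/(1 − u). That is 1 − 0.02/0.99 = 0.98 at 1% each and 1 − 0.04/0.98 = 0.96 at 2% each.

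**If rates differ between arms.** The direction is not fixed. With the same 20% and 10% risks, no mix-ups, and 5% never injected in the lower-risk arm only, the difference is 0.20 − 0.95 × 0.10 = 0.105, larger than the true 0.10.

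**Rare events.** An average factor does not describe these. A single serious event in a wrongly treated patient turns an observed count of 1 against 0 into 0 against 1.

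**The case against.** The strongest reply is that the article gives no reason to expect such patients. There is one session, given by one physician, with the syringe prepared minutes beforehand. The interval between allocation and injection is not stated. The freedom to leave is an ordinary consent right, and leaving after the only injection does not make a patient untreated. A reader might take the expected 10–20% loss in section 2.12 as evidence of dilution, but that loss is during follow-up, so it says nothing about u. It raises a separate question of missing D60 photographs. All of this stands, and it keeps the likely effect small.

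A reader might also infer that every deviation pulls the harm difference toward zero. That needs similar rates in both arms, as the working shows. It also needs the never-injected to be scored as harm-free. Pigmentation comes from post-treatment photographs and pain from a questionnaire after the session, so these patients would more probably have no value at all. The shrinkage is therefore conditional.

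Finally, because the trial looks for a difference and sets no non-inferiority margin, the as-randomised comparison remains valid, and regrouping by solution received gives up some of the protection of randomisation. That supports keeping it as a supporting analysis. It does not justify making it the only one. An analysis plan not shown may define a safety set, but such a set would conflict with a sentence that covers all analyses.

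**Conclusion.** The point holds as a minor, conditional one. The intention-to-treat sentence is stated without exception and governs a primary safety objective and all adverse events. If a few patients per arm are untreated or wrongly treated, at similar rates in both arms, the harm difference shrinks by about 3% to 6% at assumed rates of 1% to 2% each. With no deviations it does not change. Shrinkage of 15% to 20% would need 5% to 10% never injected together with 5% given the other solution, which nothing in the document suggests. The documents do not support reading the safety comparison as already biased, or intention to treat as invalid for safety. The more practical gain is correct attribution of a rare serious event, where one patient can matter.

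**What to change.** Limit the intention-to-treat sentence in section 2.12 to efficacy and add, in substance: hyperpigmentation, pain and adverse events are analysed in all patients who received any injection, grouped by the solution actually received according to the nurse's preparation record; the comparison as randomised is reported as a supporting analysis. If it is not already done, have the nurse log the product drawn against each protocol number and hold the log with the allocation list until unblinding. Settle the change before unblinding, so that the choice of population cannot look post hoc.

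The cost is one sentence and a short log kept by someone who already prepares the syringes. There are two small limits. If mix-ups occur, the safety groups are not exactly as randomised. And a log records what the nurse believes was drawn, so it cannot reveal a mix-up that goes unnoticed.
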